### Intervention and control groups

3.1

Hypertensive participants in both arms will be educated on the correct Blood Pressure (BP) measurement method at the baseline face-to-face visit. In the next (3 and 6 months since the randomization) visits, patients in the control group will be asked to bring the paper BP chart of one-week daily home measurements for documentation.

Smoking cessation pamphlets and booklets designed by THC will be presented to smoker patients in the control arm. All patients in the control arm also will receive paper-based lifestyle modification recommendations including a healthy diet and physical activity schedule.

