### The module of the app which targets HTN includes the following features

3.4

•Educational information to improve knowledge of HTN: Offering info about the risks of consequences of uncontrolled HTN and benefits of managing HTN, selecting an appropriate sphygmomanometer, guidance to choosing the size of the BP cuff according to the size of the arm circumference and standard technique of measuring BP•Educational information to improve lifestyle: Offering info on how lifestyle changes can help lower BP and reduce the risk of heart disease•Support for Self-monitoring of BP: Patients log their BP twice a day, seven days a week (using an input form with the possibility for refresh/reinsertion of information) according to the guidance of entering systolic and diastolic BP based on the monitor screen of the digital device, App keeps track of systolic and diastolic BP and shows trends with graphs and charts. Patients can view trends of their BP over time. Automatic feedback on the entered values by using color codes for specific ranges and showing alerts is provided.•Reminder functionality for improving medication adherence: Setting reminders to take medications at a specific time.

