### Definitions

3.7

•**Current cigarette smoker:** Average of ≥5 cigarettes daily use in at least the year before enrollment.•**Successful smoking cessation:** Continuous abstinence in at least 4 weeks during 6 months following up.•**Uncontrolled DLP:** Description for uncontrolled DLP will be based on the serum level of LDL-C which depends on the concomitant comorbidities including diabetes mellitus and CVD [18]. The related cut-off value for the serum level of target LDL-C is ≤ 55 mg/dL. Values more than the listed cut-off value are considered uncontrolled DLP.•**Controlled DLP**: Lowering serum level of LDL-C by < 55 mg/dL and ≥50% reduction from baseline in any of the follow-up visits at the end of 3 and 6 months from randomization and remaining controlled in the next visits during the study.•**Uncontrolled HTN:** A patient who has a history of HTN with/without using the antihypertensive drug is considered hypertensive. Participants will be considered as having uncontrolled HTN according to the ACC/AHA guidelines [19].•**Controlled HTN:** Maintaining BP below the target treatment level (130/80 mmHg) at the time of office measurements (average of 2 readings obtained on 2 separate occasions with proper patient preparation and appropriate technique) at the end of 3 and 6 months from randomization and/or during one-week daily home measurements (average of records) before clinic visits.

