### Randomization and implementation

3.10

Randomization will be performed at 7 different levels based on the type and number of risk factors the patients have (stratified randomization). Participants will be categorized into the following 7 levels; 1) Only CS, 2) Only HTN, 3) Only DLP, 4) CS + HTN, 5) CS + DLP, 6) DLP + HTN, 7) CS + HTN + DLP.

Participants in each level will be randomized into two study arms as follows.1Intervention (case) arm: Usual care + mHealth2Control arm: Usual care + paper-based recommendations and educational materials

In each level, participants will be assigned into two arms by block randomization with a 1:1 allocation using variable block sizes of 2, 4, 6, 8, and 10. Allocation of each subject to the study arms will be performed online to prevent selection bias and respect allocation sequence concealment (By concealing the allocation sequence). Allocation of each participant will be performed, just after inclusion and exclusion criteria are met and informed consent is signed by the participants. Computer-generated random number list will be utilized using permuted block stratified randomization. (Block stratified randomization Windows Version 6.0, by Steven Piantadosi, M. D., Ph.D., Cedars-Sinai Medical Center).

The practitioners who evaluate the risk factors controlling status are blinded to the group assignment.

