### Data collection and statistical analysis

3.11

We are going to record all the patient's demographic and clinical characteristics.

(Including past medical history, duration of each disease, drug and habitual history, etc.) and status of their risk factors (controlled/uncontrolled). BP, height, weight, and waist circumference will be measured during each visit. The blood sample will be taken before each visit to measure the serum level of the following factors: Creatinine, LDL-C, Glycated hemoglobin (HbA1C), Total cholesterol, High-density lipoprotein (HDL-C), Fasting blood glucose (FBS) and Triglyceride. In addition, we will request all the patients to present every laboratory test report that was done even outside THC and all other documents related to any event that required hospitalization within the last year. Hypertensive patients in the control arm will receive a paper-based chart to document their BP (systolic and diastolic) for 7 consecutive days in each month (the intervention group will also enter and save the measurements in the app).

The data will be collected from a paper questionnaire which is filled out by the research team and saved information on the digital server. Data entry will be conducted on the IBM SPSS software database.

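### Controlled hypertension may rest on office and/or home readings, with no rule between the two, and home records are kept by unblinded patients with a different tool in each arm

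*Protocol article*

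**What the plan says.** **The definition (3.7).** The office route is an "average of 2 readings obtained on 2 separate occasions with proper patient preparation and appropriate technique". The text then runs on: "at the end of 3 and 6 months from randomization and/or during one-week daily home measurements (average of records) before clinic visits". No rule covers disagreement between the two sources.

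**Its role (3.6).** The primary outcome is the number of controlled risk factors, from none to three. Hypertension control is one of the three and also enters four of the listed secondary outcomes.

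**Home records, app arm.** The hypertension module (3.4) has two entries a day, "using an input form with the possibility for refresh/reinsertion of information", with colour codes and alerts on the values entered. The app averages the week (3.2).

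**Home records, control arm.** At the 3- and 6-month visits "patients in the control group will be asked to bring the paper BP chart of one-week daily home measurements for documentation" (3.1). Section 3.11 says that hypertensive controls "will receive a paper-based chart to document their BP (systolic and diastolic) for 7 consecutive days in each month", and adds that "the intervention group will also enter and save the measurements in the app".

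**Blinding.** "The practitioners who evaluate the risk factors controlling status are blinded to the group assignment" (3.10). A cardiologist evaluates risk-factor status at the outpatient visit (3.8). Table 2 puts the app usability and satisfaction assessment in the same month 3 and month 6 columns.

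**Data quality.** Section 5 concedes, in the context of privacy worries, that patients may enter wrong values.

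**The concern.** There are two linked problems.

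First, the endpoint is not fixed. *And/or* can mean that one source is enough or that both must be below target, and the two readings give very different control rates.

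Second, the home source is not a common measuring instrument. In one arm it is part of the randomised intervention, and in the other it is a sheet of paper. Patients in both arms know their allocation and record their own values. If a favourable home average can by itself turn a patient into a success, then any difference between arms in how fully or how honestly home values are recorded passes straight into a component of the primary outcome, with no true effect on blood pressure.

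The same feature bears on blinding. If home records enter the judgement of control, whoever makes that judgement needs data whose format can identify the arm. No masking step is described.

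**Working it through.** **1. The plan's own figure.** Table 3 gives 538 per arm for hypertension (0.11 versus 0.165, 80% power, alpha 0.05, 10% loss). The usual two-proportion formula is n = [z_α√(2p̄(1−p̄)) + z_β√(p₁(1−p₁) + p₂(1−p₂))]² / (p₂−p₁)². With p̄ = 0.1375 and one-sided alpha this is (1.645 × 0.4870 + 0.842 × 0.4855)² / 0.055² = 484, and 484/0.9 = 538. The figure reproduces, so 11% is used below as the base rate. Table 3 does not say which blood pressure source that 11% refers to. Treating it as the office rate is an assumption.

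**2. What the reading of *and/or* does.** The documents give no home blood pressure data, so a simulation was run with one million patients per arm and the same true pressures in both arms. The assumptions are:
- systolic pressure only, threshold 130, between-patient SD 14
- office average of 2 readings, error SD 8/√2
- home average of k readings, error SD 9/√k
- no systematic difference between home and office values
- mean set to give 11% office control: 130 + 1.2265 × √(14² + 8²/2) = 148.5.

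With k = 7 in both arms, office control is 11.0%, *either* gives about 13.7% and *both* gives 7.2%. The wording alone moves the rate by a factor of 13.7/7.2 = 1.9.

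**3. Spurious difference under *either*.** Hypertensive patients per arm: 1544 × 0.47 × 0.9 / 2 = 327, assuming that the 47% in Table 3 applies to those enrolled. Rejection probability, two-sided 5%: 1 − Φ((1.96·se₀ − d)/se₁) + Φ((−1.96·se₀ − d)/se₁), where d is the gap, se₀ the pooled and se₁ the unpooled standard error. Example, app values 3 mmHg low: d = 0.1590 − 0.1373 = 0.0217, se₀ = se₁ = 0.0278, result 12.2%.

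| Scenario, no true effect | Control arm | App arm | Rejection |
|---|---|---|---|
| 7 readings in each arm, equal quality | 13.62% | 13.69% | 5.0% |
| 7 (paper) vs 14 (app) unbiased readings | 13.67% | 13.26% | 5.3% |
| Home records usable in 60% vs 90% | 12.60% | 13.12% | 5.4% |
| Usable in 30% vs 90% | 11.79% | 13.12% | 8.1% |
| Usable in 0% vs 90% | 10.98% | 13.12% | 13.4% |
| App values 2 mmHg too low | 13.75% | 14.90% | 7.1% |
| App values 3 mmHg too low | 13.73% | 15.90% | 12.2% |
| App values 5 mmHg too low | 13.70% | 18.44% | 37.8% |

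All rows but the first use 7 paper and 14 app readings. In the three availability rows a missing home record adds nothing, so control = office rate + availability × (*either* rate − office rate). With office pressure alone, rejection is 5.0% in every reporting scenario, and availability of home records cannot affect it.

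Without the simulation, a spurious gap of 1, 2, 3 or 5 points on a base of 11% gives rejection in 6.9%, 12.3%, 21.2% or 46.4% of trials with 327 per arm, and 7.8%, 16.0%, 29.2% or 62.5% with 484.

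These rates concern the hypertension comparison at one time point, not the four-category count.

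**4. Blinding, sections side by side.** Section 3.10 blinds the evaluators, 3.8 has control judged at the visit, 3.7 makes home records part of that judgement, and 3.1 asks only controls to bring paper. Nothing in the article says that records are transcribed or masked first.

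**The case against.** The other side has several good points.

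- **Blinding.** A reader might infer that the stated blinding fails. The article does not say so. Controls bring the chart for documentation, the research team fills in the paper questionnaire (3.11), and Table 2 does not say who runs the app questionnaire or in what order. The full protocol may describe masking. What stands is that the arrangement as described leaves the blinding unprotected.
- **Schedules.** A reader might see 3.1 and 3.11 as contradictory. A monthly charted week is compatible with bringing one week to the visit, and the addition in 3.11 about the intervention group can mean one common week. Only the two daily entries in 3.4 clearly differ, and reading count alone does not favour the app (table, second row).
- **Reminders.** The reminders in 3.4 are for taking medication. No reminder to log blood pressure is described, so they are no ground for expecting fuller app records.
- **Editing.** A paper chart can also be altered or filled in late, and 3.1 trains hypertensive patients in both arms.
- **Direction.** If *and/or* means both, fuller app records are an extra hurdle, not an advantage. This stands for completeness. Under-reporting would still favour the app under *both*, though less: 8.4%, 8.8% and 9.6% against 7.3%, 7.3% and 7.2% for shifts of 2, 3 and 5 mmHg.
- **Size.** A reader might assume home records in 95% versus 60%, and that a share q of 5% to 20% of those uncontrolled in the office pass at home. Then control = 0.11 + 0.89 × q × availability gives 15.2% versus 13.7% up to 27.9% versus 21.7%, risk ratios 1.11 to 1.29. None of these inputs is in the documents. The simulation implies q = (0.137 − 0.11)/0.89 = 0.03, which gives 13.5% versus 12.6%, risk ratio 1.07.

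**Conclusion.** The point holds in a limited form. The definition leaves open how the two sources combine, and one of them is self-recorded by unblinded patients with arm-specific tools. If either source suffices, a component of the primary outcome can differ between arms with no true effect.

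The bias is possible, not certain, and the documents do not fix its size. Under the simulation's assumptions it is modest when only completeness differs (5.4% rejection at 60% versus 90% usable, 8.1% at 30% versus 90%) and becomes large only when app values run several mmHg low (12.2% at 3 mmHg, 37.8% at 5 mmHg). These figures rest on assumed variances, equal home and office means, an 11% office rate and about 327 hypertensive patients per arm. A systematic home-office difference common to both arms would change the share who pass only at home, and so the effect of unequal completeness.

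The threat to assessor blinding is a risk that the article leaves open, not a shown failure.

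**What to change.** - In 3.7, define controlled hypertension for the primary outcome by the office measurement alone, taken by the blinded assessor. Both arms already have this measurement. State how the two occasions fit the single visit that Table 2 shows at each time point.
- Report the one-week home average as a secondary outcome, with the same week, the same readings per day and the same minimum number of readings in both arms. Reconcile 3.1, 3.4, 3.7 and 3.11 accordingly.
- Have existing research staff collect paper charts, app data and app questionnaires after the blinded assessment, and ask patients not to mention the app or the chart to the assessor.

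The cost is definition wording and a visit-order instruction. The downside is that patients controlled only on home readings no longer count in the primary outcome. Keeping home readings in the primary definition under identical rules would remove the differences written into the plan, but the tools would still differ and the values would still be self-recorded by unblinded patients. The office measurement is therefore the safer choice.

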### Participants

3.8

According to eligibility criteria (Table 1), 1544 individuals will be selected. Participants in both arms will receive their routine care and the intervention arm will be encouraged to follow guides for each risk factor using the app in addition to the routine care. After 3 and 6 months, the status of risk factors will be determined through outpatient visits and face-to-face interviews for both arms. All the participants will be visited in an outpatient clinic by a cardiologist to evaluate the status of the risk factors and document any cardiovascular events (outcomes). Any additional visits will be considered for any patient requiring fewer interval visits.

During study time, patients in the intervention arm will be encouraged to continue to use the app. The patients in both arms will be allowed to have their routine care inside and outside THC whenever needed. The participant timeline and summary of the study protocol are summarized in Table 2 and Fig. 1, respectively.

**Table 2 tbl2:** Participant timeline.

		Study period			
		Enrollment	Allocation	Post-allocation	Close-out
**Month**		−3 ± 2 days	0	3	6
**Enrollment**		×			
**Eligibility screen**		×			
**Informed consent**		×			
**Allocation**			×		
**Intervention**			×	×	×
**Assessment**	Baseline variables	×		×	×
	Measuring systolic and diastolic blood pressure	×		×	×
	Evaluating smoking status	×		×	×
	Measuring low-density lipoprotein cholesterol serum level	×		×	×
	Evaluating adherence to treatment and diet			×	×
	Evaluating the usability (data entry) and satisfaction level of software/application			×	×

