### Sample size calculation

3.9

Farkouh et al. [22] which studied pooled data obtained from large randomized trials display the success rate in controlling risk factors in CAD patients for secondary prevention through lifestyle modification and drug consumption.

To increase the success rate percentage of modifying the risk factors by at least 1.5 times, concerning significance level of α = 0.05, study power of 80% and 10% loss of samples, a sample size of 257, 538, and 772 were considered for DLP, HTN, and CS, respectively. The largest sample size of 772 which is related to CS was selected (772 × 2 = 1544). The calculation was performed by G-power software. The final results are reported in Table 3.

**Table 3 tbl3:** Success rates in controlling Dyslipidemia, Hypertension and smoking and calculated sample size.

Risk Factor	Success rate percentage in the control group	Success rate percentage in the intervention group	Sample size in each group counting 10% shedding of samples	The abundance of patients referred to the Tehran Heart Center
**Dyslipidemia**	0.2	0.3	257	0.72
**Hypertension**	0.11	0.165	538	0.47
**Cigarette smoking**	0.08	0.12	772	0.34

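### Smoking control is determined at interview from unblinded patients with no tobacco marker, so a modest arm difference in false quit claims could reproduce the planned smoking effect; the primary count is affected much less

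*Protocol article*

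**What the plan says.** Section 3.7 defines smoking success as "Continuous abstinence in at least 4 weeks during 6 months following up". On how status is established, section 3.8 says "After 3 and 6 months, the status of risk factors will be determined through outpatient visits and face-to-face interviews for both arms". In Table 2, blood pressure and LDL-C are measured, whereas smoking status is evaluated. Section 3.11 lists the blood tests as "Creatinine, LDL-C, Glycated hemoglobin (HbA1C), Total cholesterol, High-density lipoprotein (HDL-C), Fasting blood glucose (FBS) and Triglyceride"; none of these indicates tobacco exposure.

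The trial is single-blind, and section 3.10 states who is blinded: "The practitioners who evaluate the risk factors controlling status are blinded to the group assignment". Patients know whether they have the app or paper materials. The app's smoking module (3.3) sends motivational, encouraging and warning messages and provides a quit plan with a progress timeline. Control-arm smokers receive pamphlets and booklets (3.1).

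Controlled smoking is one of the three components of the primary count (3.6). It is also part of four of the eight listed secondary outcomes: smoking alone, smoking with hypertension, smoking with dyslipidaemia, and all three. It determines the total of 1544 (3.9, Table 3).

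**The concern.** The endpoint requires abstinence, but the described method can record only claimed abstinence. A visit at 3 or 6 months cannot observe four weeks of not smoking, so the information comes from a patient who knows the allocation. Blinding the assessor keeps the assessor's expectations out of the score. It does not change what the patient says.

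One arm is repeatedly encouraged and warned about quitting and shown its progress; the other holds printed material. It is plausible that pressure to report success differs by arm. Over-reporting that is equal in both arms would mostly blur the comparison. Over-reporting that is higher in the app arm moves it in the app's favour when there is no true effect. The planned smoking difference is only four percentage points, so a small reporting difference matters.

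**Working it through.** **Inputs.** From section 3.9 and Table 3: smoking success 8% (control) and 12% (app), "significance level of α = 0.05, study power of 80% and 10% loss of samples", 772 per arm, and a 34% share of smokers among patients referred to the centre. Allocation is 1:1 (3.10). The excess false-claim rate f is an assumption; the article gives no value.

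**The plan's own figure.** The usual two-proportion formula for 8% v 12% at 80% power, one-sided α = 0.05 and no continuity correction gives 695 per arm. Allowing for 10% loss, 695 / 0.90 = 772.2, which agrees with 772. The two-sided version gives 882, or 980 after loss, and does not reproduce it. The article does not state sidedness. The rejection rates below are two-sided, in line with the planned χ² tests and 95% intervals.

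**False claims needed.** Let true quitting be 8% in both arms, and let f be the excess fraction of app-arm non-quitters who claim success.

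- Observed app-arm rate = 0.08 + 0.92 × f.
- Setting this to 0.12 gives f = 0.04 / 0.92 = 4.3%.
- In people, 0.04 × 695 ≈ 28 per arm if every evaluable participant smokes, or 0.04 × 236 ≈ 9 per arm at a 34% share after loss (0.34 × 695 ≈ 236).

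The answer does not depend on controls being fully truthful. If 1% to 5% of control non-quitters also make false claims and the control arm still shows 8%, the between-arm difference needed is 4.3 to 4.1 points.

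**Chance of a significant smoking result with no true effect** (simulated two-sided 5% Pearson χ² test):

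| Smokers per arm | f = 0 | f = 2% | f = 3% | f = 4.3% |
|---|---|---|---|---|
| 772 (all smoke, no loss) | 5% | 24% | 46% | 75% |
| 695 (all smoke, after loss) | 5% | 22% | 42% | 70% |
| 262 (34%, no loss) | 5% | 11% | 19% | 33% |
| 236 (34%, after loss) | 5% | 11% | 18% | 31% |

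The rows after loss are the relevant ones, because 772 already includes the 10% allowance.

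**Effect on the primary count.** Using the Table 3 rates and shares, the bias adds about 0.34 × 0.04 = 0.014 to the mean count. The planned mean difference is about 0.72 × 0.10 + 0.47 × 0.055 + 0.34 × 0.04 = 0.111, so the bias is about 12% of it. I also simulated the 0-3 count with the control success rates of Table 3 for hypertension and dyslipidaemia in both arms. This assumed that risk factors occur independently at the Table 3 shares, with at least one present. At f = 4.3%, comparing mean counts, the false-positive risk is about 9% with 695 per arm and 10% with 772, against a nominal 5%. A χ² test on the categories gives about 8%. At f = 2% the risk is about 5-6%.

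**The case against.** **Self-report is inferred, and the article is condensed.** The article never uses the term, and a verification procedure could sit in a fuller protocol. That possibility remains. But the article gives the endpoint definition, the assessment schedule and an itemised assay list, with measured criteria for LDL-C and office blood pressure. On what is written, smoking rests on the interview.

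**The plan already shows results without smoking.** A reader might infer that nothing in the plan would expose a smoking-driven result. The text does not support this. Section 3.6 lists controlled hypertension, controlled dyslipidaemia and the two together as separate outcomes, as well as control by stratum, and three of the seven strata (3.10) contain no smokers. What is absent is an analysis of the primary count itself without smoking.

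**Blood pressure is not purely objective either.** It is tempting to set smoking against two measured components. Section 3.7 allows hypertension control to rest on home readings, which patients record themselves, on paper in one arm and in the app in the other (3.11). A recount on LDL-C and any blood pressure reading would still contain patient-recorded data. This objection stands and shapes the fix.

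**Section 5 is about privacy.** A reader might take its remark on incorrect information as an admission that quit claims will be false. It concerns patients unsure about data security and does not bear on what is said at interview.

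**The false-claim rates are assumed, and the largest rejection rates need every participant to smoke.** Both are true. The range is therefore shown, and the 34% share gives much lower figures.

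**Conclusion.** The point holds, mainly for the smoking outcome and the three combined secondary outcomes that contain it. With 8% true quitting in both arms, an excess of 4.3% false claims among app-arm non-quitters reproduces the whole planned effect. It produces a significant smoking result in about 70% of trials with 695 evaluable smokers per arm and about 31% with 236. The values of f are assumptions. The 34% share refers to referred patients; the share among those enrolled is not given and could be higher.

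A reader might go further and conclude that false quit claims could manufacture the primary result. The figures do not support that: the false-positive risk on the count rises to about 9-10% at f = 4.3% and stays near 5-6% at f = 2%. The consequence is that a positive smoking result, obtained as described, could not be told apart from arm-dependent reporting. This is worth correcting because smoking sets the sample size and the remedy is cheap. It does not invalidate the trial.

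**What to change.** 1. **Section 3.12.** Prespecify a sensitivity analysis of the primary count without the smoking component, using LDL-C and office blood pressure only, because home readings are also patient-recorded. Label the smoking result as self-reported. State that success on the count will not be claimed if it rests on smoking alone. Cost: wording and one further run of the same analysis.

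2. **Section 3.11.** For patients in both arms who report abstinence at the 3- or 6-month visit, measure cotinine in the blood already drawn. Record use of nicotine replacement and of hookah or other tobacco, since each can raise cotinine in someone who has stopped cigarettes. Report a verified-abstinence analysis in which a positive result not explained by those sources counts as not controlled. Cost: about 50 assays per visit (0.34 × 1544 ≈ 525 smokers, about 262 per arm; 262 × 0.08 + 262 × 0.12 ≈ 52), with no extra visit or blood draw. The number rises if more smokers are enrolled.

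Limit: cotinine reflects recent exposure only. The definition in 3.7 also credits a four-week quit that ended before the visit. Such quits stay unverified and should be reported separately.
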